## Abstract

**Introduction:**

Preterm birth complicates >15 million pregnancies annually worldwide. In many countries, women who present with signs of preterm labour are treated with tocolytics for 48 hours. Although this delays birth, it has never been shown to improve neonatal outcome. In 2015, the WHO stated that the use of tocolytics should be reconsidered and that large placebo-controlled studies to evaluate the effectiveness of tocolytics are urgently needed.

**Methods and analysis:**

We designed an international, multicentre, randomised, double-blinded, placebo-controlled clinical trial. Women with threatened preterm birth (gestational age 30–34 weeks), defined as uterine contractions with (1) a cervical length of < 15 mm or (2) a cervical length of 15–30 mm and a positive fibronectin test or (3) in centres where cervical length measurement is not part of the local protocol: a positive fibronectin test or insulin-like growth factor binding protein-1 (Actim-Partus test) or (4) ruptured membranes, will be randomly allocated to treatment with atosiban or placebo for 48 hours. The primary outcome is a composite of perinatal mortality and severe neonatal morbidity. Analysis will be by intention to treat. A sample size of 760 participants (380 per group) will detect a reduction in adverse neonatal outcome from 11.95% to 6% (alpha error 0.05, beta error 0.2). A cost-effectiveness analysis will be performed from a societal perspective.

**Ethics and dissemination:**

This study has been approved by the Research Ethics Committee (REC) of the Amsterdam University Medical Centres, location AMC, as well as the REC’s in Dublin and the UK. The results will be presented at conferences and published in a peer-reviewed journal. Participants will be informed about the results.

**Trial registration number:**

Nederlands Trial Register (Trial NL6469).

Strengths and limitations of this studyThe primary outcome is perinatal mortality and neonatal morbidity, not prolongation of pregnancy.This is the largest randomised trial comparing atosiban to placebo for women with threatened preterm birth.Over 40 hospitals in Europe will participate.Tocolysis is incorporated in daily routine as it has been the recommendation in many guidelines.It will prove to be a challenge in counselling patients to participate in a placebo controlled trial, especially in an acute setting.

## Introduction

Preterm birth, defined as birth before 37 weeks’ gestation, is a major contributor to perinatal mortality and morbidity, complicating over 15 million pregnancies worldwide.^1 2^ Of all infant deaths before the age of 5 years, more than one-third can be attributed to preterm birth.^3^ In addition, spontaneous preterm birth is the leading cause of neonatal morbidity, mostly due to respiratory immaturity, intracranial haemorrhage and infections.^4 5^ These conditions can have long-term neurodevelopmental sequelae such as cognitive impairment, cerebral palsy and visual and hearing deficiencies. Preterm birth is one of the largest single contributors to the global burden of disease because of the high mortality early in life and the morbidity of lifelong impairment.^6^

Maternal administration of corticosteroids to accelerate fetal lung maturation is an effective treatment for women with threatened preterm birth.^7^ Since steroids have their maximum effect if birth is delayed by 48 hours, many obstetricians administer a tocolytic drug alongside the steroids to allow maximal steroid effect and facilitate transport of the mother to a centre with neonatal intensive care unit facilities if needed. Several tocolytics are used, including β adrenoceptor agonists, cyclooxygenase inhibitors (COX), magnesium sulfate, calcium-channel blockers and oxytocin receptor antagonists. Though more or less effective in delaying delivery, no tocolytics used in obstetrical practice are proven effective in reducing neonatal morbidity and mortality.^8 9^ None of the studies so far have been powered to show such an effect.

The two most commonly used tocolytic drugs, atosiban and nifedipine, showed comparable perinatal outcome in the APOSTEL 3 study.^10^ However, neonatal mortality was higher in the nifedipine group, although not significant (5.4% vs 2.4% relative risk (RR) 2.20; 95% CI 0.91 to 5.33).

The oxytocin receptor antagonist atosiban has fewer maternal side effects in head to head comparison with alternative drugs,^11^ and showed similar effectiveness in delaying birth compared with ritodrine.^12^ In placebo-controlled trials, a Cochrane review showed that atosiban did not reduce perinatal mortality (RR 2.25, 95% CI 0.79 to 6.38; two studies with 729 infants) or major neonatal morbidity,^13^ although the quality of this review has been questioned.^14^

One explanation might be that since spontaneous preterm birth is associated in 40%–70% of cases with chorioamnionitis,^15 16^ tocolysis may prolong fetal exposure to an infectious environment, which may worsen neonatal outcome.

Perinatal outcome has also markedly improved over the last few decades, in part due to postnatal interventions such as exogenous surfactant treatment which reduces mortality and respiratory morbidity in preterm infants.^17^ This might also limit the potential benefit of tocolytics.

Worldwide, practice varies widely. Several large institutions in countries like Canada, Scotland and Ireland, rarely use tocolytics, while in the USA, COX (indomethacin) and calcium channel blockers (nifedipine) are popular. In Europe, nifedipine and the oxytocin antagonist, atosiban, are both widely used.

In conclusion, current widespread use of tocolytic drugs for this indication is not supported by the available evidence. The primary goal of tocolysis should not be prolongation of pregnancy, but improvement of neonatal outcome. This view is supported by the WHO, as they state in their 2015 guidelines on preterm birth that the effectiveness of tocolytics is not proven, and that placebo-controlled studies are urgently needed.^18^ Based on the results of the APOSTEL 3 study,^10^ the associated editorial,^19^ and its safety profile we chose to evaluate atosiban in the APOSTEL 8 study.

### Objective

To test the hypothesis that tocolysis with atosiban in late preterm birth (30–34 weeks) reduces neonatal mortality and morbidity and is cost-effective compared with placebo.

## Methods and analysis

### Design and setting

We will conduct an international, multicentre, double-blind, randomised, placebo-controlled clinical trial, performed in The Netherlands, UK and Ireland.

### Participants/eligibility criteria

Women, aged ≥18 years, with threatened preterm birth and a gestational age between 30^+0^ and 33^+6^ weeks are eligible. Threatened preterm birth is defined as uterine contractions with

A cervical length of <15 mm orA cervical length of 15–30 mm and a positive fibronectin test orIn centres where cervical length measurement is not part of the local protocol: a positive fibronectin test or insulin-like growth factor binding protein-1 (Actim-Partus test) orRuptured membranes.

These inclusion criteria are based on the results and conclusions of the APOSTEL 1 study^20^ and current guidelines within the Netherlands and the UK. Moreover, our previous APOSTEL 3 study, with resembling inclusion criteria, showed that half of the women with these criteria deliver within 7 days,^10^ validating this definition of women at high risk for preterm birth. In addition, the sample size of expected adverse neonatal outcome in the gestational age group of 30–34 weeks, was calculated from the APOSTEL 3 study.

This study was designed in a pragmatic fashion, in order for the results to be applicable in the current clinical practice. As most national guidelines and local protocols propose treatment for threatened preterm birth in both singleton and multiple pregnancies, as well as women with ruptured membranes, all these categories of patients are eligible for the study.

Women with a contraindication for tocolysis, signs of fetal distress, clinical signs of intrauterine infection, previous treatment for threatened preterm birth with corticosteroids in the current pregnancy and known fetal chromosomal or severe structural abnormalities are not eligible.

### Procedures, recruitment, randomisation and collection of data

Potential participants will be identified by the local research co-ordinators and/or the staff of participating hospitals. Women eligible for the trial will be counselled by doctors, midwifes or research nurses trained in ‘good clinical practice’, and will be given a patient information form to read. Those who wish to participate, will be asked to give for written informed consent and are registered within the central trial database. Randomisation will be performed by using sequentially numbered medication packs available in each centre. Only the independent data manager has access to the computer-generated randomisation list in which the medication numbers are linked with atosiban or placebo. Treatment allocation is blinded to investigators, participants, clinicians and research coordinators. Randomisation will be balanced with varying block sizes of 2 and 4, and stratified by centre.

At study entry, baseline demographic, prior obstetric and medical history will be recorded into the web-based case report form accessible through a secure central website (Castor Electronic Data Capture, Ciwit B.V.).^21^ Details of delivery, maternal and neonatal assessments during pregnancy and postpartum period will be recorded on the same system. All data will be coded, processed and stored with adequate precautions to ensure patient confidentially. This is described in a separate data management plan.

### Interventions

Participants are allocated to atosiban or matching placebo (0.9% saline) for 48 hours. The medication will be administered by a bolus injection of 6.75 mg/0.9 mL in 1 min followed by a continuous infusion of 18 mg/hour for 3 hours followed by a continuous infusion of 6 mg/hour for the remaining 45 hours. Participating women will otherwise be treated according to local protocol based on national guidelines, including corticosteroids MgSO_4_ for neuroprotection and antibiotics if needed.

### Outcome measures

Outcome parameters are in line with the core outcome set for studies on prevention of preterm birth defined by members of GONet and the Core Outcomes in Women’s health (CROWN) initiative (www.crown-initiative.org).^22^

The primary outcome measure is a composite of adverse perinatal outcome composed of perinatal in-hospital mortality and six severe perinatal morbidities: bronchopulmonary (BPD), periventricular leucomalacia (PVL) >grade 1, intraventricular haemorrhage >grade 2, necrotising enterocolitis (NEC) ≥stage 2, retinopathy of prematurity >grade 2 or needing laser therapy, and culture proven sepsis.

The diagnosis of BPD will be made according to the international consensus guideline as described by Jobe and Bancalari.^23^ PVL >grade 1 and intraventricular haemorrhage >grade 2 will be diagnosed by repeated cranial ultrasound according to the guidelines on neuroimaging described by de Vries *et al*^24^ and Ment *et al*.^25^ NEC ≥stage 2 will be diagnosed according to Bell *et al*.^26^ Culture proven sepsis is diagnosed on the combination of clinical signs and positive blood cultures. The components of the composite adverse perinatal outcome will also be assessed separately.

Secondary infant outcomes will be birth within 48 hours, time to birth, gestational age at birth, birth weight, number of days on invasive mechanical ventilation, length of neonatal intensive care unit (NICU) stay, convulsions, asphyxia, meningitis, pneumothorax until hospital discharge.

Maternal outcomes will be mortality, infection of inflammation and harm to mother from interventions (side effects). Side effects are defined as admission to intensive care, anaphylactic shock, dyspnoea, hypotension (leading tocardiotocography abnormalities), liver test abnormalities (elevated aspartate aminotransferase (ASAT) or alanine aminotransferase (ALAT)), general side effects (nausea, vomiting, headache), postpartum haemorrhage defined as >500 mL blood loss and maternal mortality.

We will ask informed consent to approach the parents for long-term follow-up of the children. We intend, subject to funding, to use standardised questionnaires at 2 and 5 years of age.

Maternal quality of life will be assessed at randomisation and at 3 months baby corrected age using the EuroQol (EQ-5D-5L) questionnaire. This consists of five dimensions (mobility, self-care, usual activities, pain/discomfort, anxiety/depression) that are rated using five levels (no problems, slight problems, moderate problems, severe problems, extreme problems).

Societal costs will be assessed using adapted versions of the iMTA Medical and Productivity Cost Questionnaires at 3 months corrected baby age. Cost data include costs of the intervention, other healthcare utilisation, patient and family costs and costs of productivity losses.

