### Withdrawal of subjects

Participants can cease study treatment at any time for any reason if they wish to do so. Unless they refuse to allow further data collection, such participants will continue to be followed-up and will be analysed in the group to which they were originally allocated. Participants who decline follow-up will have no further trial data collected. Any results collected up to the point at which they decline follow-up will be analysed. Study medication will be discontinued in patients with signs of intrauterine infections or signs of fetal distress (abnormal CTG, meconium stained amniotic fluid). Data of such participants will continue to be analysed. Further management will be left to the expertise of the responsible clinician. The responsible clinician can contact a perinatologist from the project group in case of suspected side effects or other medical problems. If necessary, treatment will be discontinued.

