### Monitoring and safety

An independent data safety monitoring board (DSMB) will focus on both effectiveness and safety. Serious adverse events (SAEs) will be collected from the first study-related procedure until 3 months after delivery. All SAEs will be reported to the DSMB within 7 days. Whenever there is proof of effectiveness (at interim analysis) or safety issues (increased (serious) adverse events in one of the two treatment arms) the DSMB will advise whether the trial should be stopped or continued. The DSMB will be blinded when first analysing the data, but unblinded before reaching a decision.

The advice(s) of the DSMB will only be sent to the sponsor of the study. Should the sponsor decide not to fully implement the advice of the DSMB, the sponsor will send the advice to the reviewing Medical Ethics Committee, including a note to substantiate why (part of) the advice of the DSMB will not be followed.

A formal interim analysis is planned after data collection of 500 women. At these interim analyses, the Haybittle-Peto alpha spending function will be used, which means that an effect at interim with a p value <0.001 is considered statistically significant.

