### Statistical analysis

#### Data analysis

Data analysis will be performed according to the intention-to-treat principle. In the baseline table, categorical variables will be expressed as a number with the percentage of the total allocation arm. Continuous variables will be presented as mean with SD, as geometric mean with 95% CI or as median with IQR, whichever appropriate.

The main outcome ‘adverse neonatal outcome’ will be assessed on the infant level, using a log-binomial generalised estimating equations model to take into account the correlation of outcomes in multiples, resulting in an RR with accompanying 95% CI. To account for stratified randomisation by centre, we will also take centre into the model if the model converges.^29^ We will account for interdependence between outcomes in multiple pregnancies by considering the mother as a cluster variable.^30^

The other secondary outcome measures on the child level will be analysed similar to the primary outcome measure. Outcomes on the maternal level will be assessed by using a binomial regression model with log-link function. When a statistically significant difference in primary outcome is found between both groups, we will calculate the number needed to treat. Time to delivery will be evaluated by Kaplan-Meier estimates and Cox proportional hazard analysis, taking into account the different durations of gestation at study entry, and will be tested with the log rank test. A p value of <0.05 will be considered to indicate statistical significance.

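### Hypotension counts as a maternal side effect only when it leads to CTG abnormalities, so non-serious maternal hypotension without a fetal sign drops out of the comparison between arms

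*Protocol article*

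**What the plan says.** Under Outcome measures, the protocol article names the maternal outcomes: "Maternal outcomes will be mortality, infection of inflammation and harm to mother from interventions (side effects"). It then defines the last of these by a list: "Side effects are defined as admission to intensive care, anaphylactic shock, dyspnoea, hypotension (leading tocardiotocography abnormalities), liver test abnormalities". The list ends with "general side effects (nausea, vomiting, headache), postpartum haemorrhage defined as >500 mL blood loss and maternal mortality". (A space is missing in the hypotension item; the bracket plainly means leading to cardiotocography abnormalities.)

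The Data analysis section says how such outcomes are compared: "Outcomes on the maternal level will be assessed by using a binomial regression model with log-link function".

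The Monitoring and safety section adds a second route for harms: "Serious adverse events (SAEs) will be collected from the first study-related procedure until 3 months after delivery". The data safety monitoring board is to consider "safety issues (increased (serious) adverse events in one of the two treatment arms").

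**The concern.** The outcome is harm to the mother, yet one item on its list is met only if the fetus shows a monitoring change. A woman whose blood pressure falls during the infusion, with symptoms but a normal CTG, has no hypotension event. The article does not explain the restriction.

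Tolerability is part of the case for the drug. The Introduction states: "The oxytocin receptor antagonist atosiban has fewer maternal side effects in head to head comparison with alternative drugs", and it gives the safety profile as one reason for choosing atosiban. The article also describes the trial as the largest comparison of atosiban with placebo. A blinded placebo comparison of this size is a good opportunity to estimate the absolute maternal risk of the drug, and the definition discards part of that information. If sites record hypotension only as the article defines it, a later analysis plan cannot recover the missing events.

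**Working it through.** **1. Is the bracket a condition or a comment?** The neighbouring brackets in the same sentence specify their items: liver test abnormalities means raised ASAT or ALAT, and general side effects means nausea, vomiting and headache. Read the same way, the bracket after hypotension limits which hypotension counts.

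**2. Is the uncounted hypotension caught elsewhere?**

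| Route | What it catches | Non-serious hypotension, CTG unchanged |
|---|---|---|
| Hypotension item | Hypotension leading to a CTG abnormality | No |
| Intensive care admission, anaphylactic shock, maternal mortality | The extreme cases | No |
| Dyspnoea, nausea, vomiting, headache | The symptom, if she has one | Only as that symptom, not as hypotension |
| Serious adverse event reporting | Events meeting seriousness criteria | No |
| Safety board review | Adverse events by arm | Does not change the outcome definition |

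What is left out is therefore non-serious maternal hypotension without CTG change.

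**3. What does the restriction do to the comparison?** Let p1 and p0 be the true proportions with hypotension on atosiban and placebo, and let f1 and f0 be the fractions of those women whose hypotension leads to a CTG abnormality. The trial counts f1·p1 and f0·p0.

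- Counted risk ratio = (p1/p0) × (f1/f0). With f1 = f0 it equals p1/p0.
- Counted risk difference = f1·p1 − f0·p0. With f1 = f0 = f it equals f × (p1 − p0), which is smaller in size whenever f is below 1.
- Standard error of the log risk ratio with n women per arm = √[1/(n·f·p1) − 1/n + 1/(n·f·p0) − 1/n], which grows as f falls.

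**4. Illustration.** The documents give neither hypotension rates nor f. The values here are assumptions that show only how the effect works: p1 = 4%, p0 = 1%, f equal in both arms. The 380 per arm is from the Sample size section. Expected counts are 380 × 0.04 × f and 380 × 0.01 × f. The interval is 4.0 divided and multiplied by exp(1.96 × SE).

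| f | Expected counts | Risk ratio | Risk difference | SE of log risk ratio | Approximate 95% interval for the risk ratio |
|---|---|---|---|---|---|
| 1 (all counted) | 15.2 v 3.8 | 4.0 | 3.0 points | 0.57 | 1.3 to 12.2 |
| 0.5 | 7.6 v 1.9 | 4.0 | 1.5 points | 0.81 | 0.8 to 19.5 |
| 0.2 | 3.0 v 0.8 | 4.0 | 0.6 points | 1.28 | 0.3 to 49 |

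For example, at f = 0.2: SE = √(1/3.04 − 1/380 + 1/0.76 − 1/380) = √1.639 = 1.28. With counts this small the intervals are rough. The risk ratio stays at 4.0, the absolute difference shrinks in proportion to f, and the interval widens. If the drug does not raise the rate of hypotension, there is no excess to miss, and the only loss is a less precise estimate.

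**The case against.** The strongest defence is that the bracket is a deliberate threshold for clinical relevance. It is stated openly, it applies to a maternal safety list rather than the primary outcome, and it contradicts nothing else in the article. The severe cases are caught by other routes, and symptoms such as nausea or dyspnoea count under their own items. Nothing in the document suggests that atosiban causes hypotension.

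Most of this stands, and it limits the importance of the point. The threshold reading itself fits poorly: the same list counts nausea, vomiting and headache with no severity condition, and a fetal trace does not grade the severity of a maternal event.

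A reader might also infer stronger criticisms that the document does not support:

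- *That an abnormal CTG from another cause turns mild hypotension into an event.* The wording requires the hypotension to lead to the abnormality; coincidence does not qualify.
- *That events are lost because an abnormal CTG also stops study medication.* Withdrawal of subjects does list "signs of fetal distress (abnormal CTG, meconium stained amniotic fluid") as grounds for discontinuation, but says that the data of these participants are still analysed.
- *That symptoms arising long after the infusion are counted as side effects.* The article gives no time window for the other symptoms, but a condensed article may leave this to the full protocol or analysis plan. The outcome is also worded as harm arising from the interventions.

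**Conclusion.** The point holds in a limited form. As defined, non-serious maternal hypotension without a CTG change is left out of the comparison of maternal side effects. This costs events and precision, and it understates the absolute risk difference if atosiban does raise the rate.

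A reader might infer that the definition biases the comparison towards no difference. The document does not support that for the planned analysis. The log-link binomial model estimates a risk ratio, which is unchanged when hypotension leads to CTG abnormalities equally often in both arms. It would be distorted only if those fractions differed, and nothing in the article says that they do, or in which direction.

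The size of the loss cannot be derived from the document; the illustration rests wholly on assumed rates. The primary outcome, the sample size and the primary analysis are unaffected. This is a worthwhile, inexpensive improvement to a stated rule.

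**What to change.** Replace the hypotension item with all maternal hypotension during the study infusion, under one stated definition chosen by the trial team, and report it by arm. Keep hypotension leading to CTG abnormalities as a reported sub-category, so the category the article now defines is still available. Carry the same wording into the case report form and the statistical analysis plan.

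The cost is a change to one outcome definition and to the matching case report form item. The downside is that sites will record more events, most of them mild. The article does not describe how blood pressure is monitored during the infusion, so the team should confirm that existing measurements are enough to apply the definition in the same way at all centres.
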